### Theoretical aspects, hypothesis

#### Module 1 resource (mis-)utilization & allocation

We hypothesize that implementing the “In-HospiTOOL” in a nationwide multicenter setting will significantly shorten length of hospital stay without compromising patient outcomes and functional independence. Systematic early determination of clinical stability, estimation of the post-acute care referral probability (using the Post-acute care discharge [PACD] score [15]), fixing a possible discharge date after initial ED assessment as well as a tight interprofessional collaboration enabled through an electronical communication platform (“Visitentool”, Fig. 1) will result in decreased waiting times contributing to the shortening of length of hospital stay [16–18].

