#### Difference in differences

To quantify an overall effect on length of hospital stay after implementing the “In-HospiTOOL”, we fit a patient-level multivariate linear regression model. It will include lengths of hospital stay of “control” hospitals, all risk adjusters listed above in the manuscript, and a time variable for study weeks. The dependent variable will be length of hospital stay (days in hospital). We will test for interaction between the intervention period and the intervention population and will assess whether there is a difference in the change (slope) in length of hospital stay over time between the two study populations. The intervention and control groups will have different baseline characteristics, however both groups will be exposed to similar alterations in outcomes over time without the interventional program.

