#### Interrupted time series (ITS) model

We will analyze the trends in length of hospital stay from start of observation through the end of the intervention period (18 months). For this purpose, we will conduct an ITS as a sensitivity analysis. We will implement the ITS using generalized estimating equations (GEE), to examine linear trends in weekly, hospital-level, risk-adjusted length of hospital stays. ITS models will be tested for autocorrelation to control for seasonal trends using the Durbin-Watson statistics [25]. We will analyze the change in trend between all three time periods. This approach allows us to distinguish between a possible effect of the intervention and a difference from underlying trends facing both study groups and can also help to analyse whether the intervention effects will sustain over time. We will calculate weekly-adjusted length of hospital stay using linear GEE that includes all lengths of hospital stay from the control and intervention populations and all above mentioned risk factors. We will graph weekly length of hospital stay for all populations over time and use the estimated weekly means for control and intervention patients to assess for a weekly difference between the two groups. Finally, we explore whether the adjusted weekly length of hospital stay decreases in the intervention period and whether there will be an independent time trend effect induced by the intervention only [26].

To summarize, we will use four statistically hypothesis tests during each period: (i) Are there significant trends in length of hospital stay change during the period. (ii) Will the trend differ between the control and intervention populations (the interaction between time and control or intervention conditions) during the period. (iii) Will the trend during the intervention period differ from the trend during the observation period within all three conditions. (iiii) Will the magnitude of the altered trend between the intervention and the observation period differ between the three conditions (the interaction between the change in slope and intervention or control conditions). These models will also be implemented for the analyses of the secondary endpoints.

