Our study has several potential limitations. First, inclusion of about 35`000 patients over the 18-month study time frame is ambitious. However, based on our large experience from previous multicenter studies, a well-established multicenter research network, and the high prevalence of hospitalized multimorbid patients eligible for this trial, we are convinced that the trial is feasible. The second limitation of this trial is the lack of randomization. Methodologically, in a trial whose intervention focuses on the process of care, neither patient-level randomization nor a randomized cross-over design was feasible as a carry-over effect would have biased the control group. For a cluster randomized trial, a large number of similar clusters (i.e. hospitals) would be needed – which is challenging in Switzerland particularly in light of the limited study budget. Therefore, we chose an ITS model in a quasi-experimental study design using administrative data from non-participating hospitals as a control group. Doing so, we account for differences in the patient population that may occur due to epidemiological variations. Third, as a pragmatic trial with a bundled intervention, it will be challenging to understand which part of our intervention shows clinical effects, leading to potential participation bias. Nonetheless, the large amount of health care data collected will also allow to provide scientific evidence as to which elements of patient management are influenced by the intervention.

In conclusion, this pragmatic comparative effectiveness health services research trial will inform whether the implementation of a novel electronic tool for inpatient management optimizes inter-professional collaboration and thereby reduces length of hospital stay without derogating subjective and objective patient-oriented measures. Our trial will help to compare between diverse transition processes within seven different hospitals and to create a benchmarking for inpatient care quality. This study synergizes national networks and, thus, has the potential to become a cornerstone in the present public healthcare discussion.

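### The four listed ITS tests look only at slopes and two of them name three conditions where two populations exist, while the DiD sentence does not say whether level or slope decides the primary endpoint

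*Protocol article*

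**What the plan says.** The Module 1 hypothesis in the protocol article is that the tool "will significantly shorten length of hospital stay without compromising patient outcomes and functional independence".

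The section Difference in differences assigns the overall effect on length of stay to a patient-level regression. It tests the interaction of intervention period and intervention population. The same sentence goes on to say that the authors "will assess whether there is a difference in the change (slope) in length of hospital stay over time between the two study populations".

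The section Interrupted time series (ITS) model says "we will conduct an ITS as a sensitivity analysis" and closes with a list: "we will use four statistically hypothesis tests during each period".

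- First: "i) Are there significant trends in length of hospital stay change during the period".
- Second: "ii) Will the trend differ between the control and intervention populations (the interaction between time and control or intervention conditions) during the period".
- Third: "iii) Will the trend during the intervention period differ from the trend during the observation period within all three conditions".
- Fourth (numbered iiii): whether the size of that change in trend differs between the three conditions. Its own bracket names only intervention and control.

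The section then carries these models over to the secondary endpoints. Before the list, it also plans a weekly comparison of estimated means between the two groups and an exploration of whether adjusted stay decreases in the intervention period. The Discussion describes the design with the words "we chose an ITS model in a quasi-experimental study design".

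**The concern.** A shorter stay is a statement about level; every listed ITS test is a statement about slope. The design makes a flat, lower series a plausible form of success. The Data collection process section sets aside a six-month run-in for technical set-up, training and pilot testing, so the tool may already be at full effect when the intervention phase begins. A series that has dropped and then stays level has no change in slope between observation and intervention.

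Three things are at stake. The sensitivity analysis could seem to contradict a correct positive primary result, and the same would apply to each secondary endpoint. Because the DiD sentence joins a level test and a slope test without ranking them, the decisive contrast for the primary endpoint is open. And the fourth test, the only controlled observation-versus-intervention contrast in the list, cannot be specified as written, because its text counts three conditions and its bracket names two.

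**Working it through.** **Plan's own figure.** The only size figure is an accrual estimate of about 35,000 patients over 18 months. From 2,500 to 8,000 patients per site and year, 7 × 2,500 × 1.5 = 26,250 and 7 × 8,000 × 1.5 = 84,000, so 35,000 lies in range. The article gives no alpha, power, effect size or SD, so there is no power figure to reproduce.

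**Assumptions (not in the article).** Two-sided alpha 0.05; three phases of 26 weeks (78 weeks); SD of stay 6 or 9 days; three control patients per intervention patient; independent weeks; no between-site variation; a sustained drop d of 0.3, 0.5 or 1.0 day.

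**Step 1: what the slope contrasts see.** Suppose there is no underlying trend difference and the drop is complete by the start of the intervention phase. The observation slope is 0 and the intervention slope is 0, so the change in slope is 0 − 0 = 0 for any d. Simulation (2,000 runs per setting, own level and slope in each phase) agrees:

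- Drop as a sudden step: all four ITS tests, and the slope part of the DiD, reject in about 4–6% of runs, up to d = 1.0.
- Drop built up linearly over the implementation phase: the third and fourth tests still reject in about 5%. The first and second tests within the implementation phase reject in 73% and 60% (d = 0.5, SD 6).
- No level terms (one continuous bent line), step of 0.5 day: the step leaks into the slopes, and the third and fourth tests reject in about 55–69%.

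The article does not say whether level terms are in the model, so what these tests detect depends on that choice.

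**Step 2: what the DiD level contrast sees.** Patients per week: 35,000 / 78 = 449. SD of the weekly group difference: SD × √(1/449 + 1/1,346) = 0.327 day (SD 6) or 0.491 day (SD 9). SE of the phase-mean contrast: multiply by √(2/26) = 0.277, giving 0.091 and 0.136.

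| d (days) | SD 6: formula / simulated | SD 9: formula / simulated |
|---|---|---|
| 0.3 | 0.91 / 0.90 | 0.60 / 0.58 |
| 0.5 | 1.00 / 1.00 | 0.96 / 0.95 |
| 1.0 | 1.00 / 1.00 | 1.00 / 1.00 |

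**Step 3: which level contrast to add to the ITS.** The usual extrapolated step projects the observation trend (centre week 13.5) to week 53 and compares it with the intervention fit (centre week 65.5). With Sxx = 26 × (26² − 1)/12 = 1,462.5, the variance factor is (1/26 + 39.5²/1,462.5) + (1/26 + 12.5²/1,462.5) = 1.105 + 0.145 = 1.251, and its root is 1.118. That is 1.118 / 0.277 = 4.0 times the SE of the phase-mean contrast. Simulated power falls to 0.13 / 0.27 / 0.77 (SD 6) and about 0.08 / 0.14 / 0.45 (SD 9) for 0.3 / 0.5 / 1.0 day.

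**Step 4: the reference phase in the DiD.** The text does not say what the intervention period is compared with. If all other weeks formed the reference, with equal phases, a drop built up linearly over implementation would average d/2 there. The reference would then contain (0 + d/2)/2 = d/4, and the contrast would return 0.75d. A drop at the start of implementation would return d − (0 + d)/2 = 0.5d.

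**Step 5: the conditions.** The DiD section speaks of two study populations; the second ITS test and the bracket of the fourth name control and intervention. Only the phases number three. Three conditions occurs in the third and fourth tests alone and has no referent.

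**The case against.** The strongest reply is that the primary analysis already has the right test. The DiD is given the task of quantifying the overall effect, its period-by-population interaction is a level contrast, and Step 2 shows that it would find a sustained drop. The ITS is only a sensitivity analysis, its trend tests serve the stated aim of seeing whether effects last, and its text also compares weekly means. Model terms such as a step are often left to an analysis plan.

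Most of this stands, and it rules out several stronger readings that a reader might infer:

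- That a sustained drop would be scored as no effect by the trial. It would not; the DiD interaction would detect it.
- That the stated tests have no power. A gradual fall shows in the first and second tests during implementation, and a model without level terms would turn a step into a slope change.
- That all four tests refer to three conditions. Only the last two do.
- That the number of tests inflates the false-positive rate of the primary claim. These are overlapping contrasts of the same slopes in a sensitivity analysis, several of them descriptive, and not independent routes to that claim.
- That the ITS has contradictory status. The Discussion describes the design and the ITS section assigns the analysis rank; one consistent label would help, but the tension is slight.

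What the reply does not remove: the article itself fixes a list of formal tests, all on slope, and extends the models to the secondary endpoints. The comparison of weekly means stands outside that list. Nor does the reply settle which half of the DiD sentence decides.

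**Conclusion.** The point holds in a limited form. The formal ITS tests do not match the hypothesis. If the effect is complete by the start of the intervention phase and then flat, and each phase has its own level, the third and fourth tests reject at about alpha (about 5%) for drops up to 1.0 day, while the DiD interaction has power of 0.90–1.00 (SD 6) or 0.58–1.00 (SD 9). The likely harm is a supportive analysis that appears to contradict a true positive result, and the same mismatch in the secondary endpoints; it is not a missed primary effect. Separately, the primary contrast is left open between level and slope, and three conditions is an error of wording.

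The power figures rest on assumed SDs, an assumed control ratio and independent weeks without clustering, so they are optimistic. The near-alpha result for the third and fourth tests does not depend on the SD, because the quantity they test is zero.

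**What to change.** 1. In the DiD section, name one primary contrast: the group-by-phase level interaction, intervention phase versus season-matched observation phase. Give the implementation phase its own indicator so that it stays out of the reference. State that the slope comparison is secondary.
2. In the ITS, add a between-group level contrast, defined as the difference in adjusted phase means and not only as an extrapolated step, whose SE is about four times larger. State that the model has a level term for each phase. Keep group-by-slope change as a secondary test of sustainability.
3. In the third and fourth tests, replace three conditions with the intervention and control populations.
4. Label the ITS as supportive throughout, and apply the same order of contrasts to the secondary endpoints.

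The cost is protocol and analysis-plan wording and some analysis code. No new data are needed.

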#### Control population

For our statistical approach as outlined below, we request data from the Federal Statistical Office to provide a nationwide comparability. We will use data on length of hospital stay. Age, gender, health care insurance, place of residence, main diagnosis, comorbidities, and study center will be used for statistical adjustment.

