**Fig. 1 Fig1:**
[figure not shown]
The “*Visitentool*” (german for “ward-round tool”). Inter-professional collaboration via an electronical communication platform. Nursing and physician staff as well as social services daily assess the clinical and functional situation about possible discharge (using simple, intuitive color coding) and propose possible discharge dates. Also, reasons for delays in discharge are being monitored

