### Endpoints

All patients will be daily assessed during hospitalization and contacted 30 days after admission by phone for a structured and blinded interview to assess primary and secondary endpoints.

The primary endpoint of this study is length of hospital stay within 30 days after admission including readmissions during this period (corresponding to Module 1). Length of hospital stay will be verified based on hospital data for the index hospital stay and complemented by 30-day interviews regarding possible secondary hospitalizations.

Secondary endpoints (corresponding to Module 1–3) include measures of patient-oriented outcomes:in-hospital and all-cause 30-day mortalityunplanned readmissions or unplanned general practitioner / ED visitsdelaying factors of ED- and medical ward’s floweffective time to hospital discharge after involving external institutions (time from transfer application to transfer)institutionalizationsatisfaction with ED-, ward-, and discharge processfunctional status (incl. Quality of life) using the EuroQol Group 5-Dimension Self-Report Questionnaire (see Additional file 1) [23].

To study hospital internal processes and effects of interprofessionality, we will look at compliance and agreement of the three health professions (physicians, nursing, and social workers) in the use of “In-HospiTOOL”, and delays from the anticipated to the effective discharge date as compared to discharge date anticipated by the different health care professionals on admission and during the course of the hospital stay. We will use the above-mentioned outcome data set as benchmark to establish a risk-adjusted resource and quality cockpit to compare different hospitals and demographics (corresponding to Module 3).

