### Statistical analysis plan and sample size

The primary analysis population includes all consecutively recruited patients following an intention-to treat (ITT) principle. The number of patients lost to follow-up will be minimized by every effort. The per-protocol (PP) population analysis will be prospectively defined to exclude patients in whom major protocol violations have occurred. Specifically, the following criteria will lead to exclusion from the PP population: major violation of study inclusion or study exclusion criteria, patients with missing information from the In-HospiTOOL forms, or missing follow-up interviews.

We will compare all endpoints between all three study phases in the overall ITT population, the PP population and within predefined subgroups as discussed below. We will analyze all endpoints in an adjusted manner for the main covariates such as age, gender, health care insurance, home of residence, main diagnosis, comorbidities, and study center. Regarding sample size considerations, we include consecutive patients in each hospital over a 6-month period for the observation, implementation, and the intervention period, respectively. Given the large number of patients per study site seen in routine (i.e. between 2`500 and 8`000 polymorbid medical inpatients) per year, we estimate to enroll approximately ~ 35′000 patients over 18 months of recruitment. This large amount of patient data will provide adequate power to investigate the effect of introducing a patient care tool in the overall medical hospitalized patient population and allow for subgroup analyses, as well as important post-hoc analyses.

We will perform two complementary, quasi-experimental analyses to estimate the effect of the intervention: difference in differences and ITS.

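### The control-based models are promised for every secondary endpoint, but length of stay is the only control outcome named, and interview endpoints cannot have a control series

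*Protocol article*

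**What the plan says.** The section on the control population in the Protocol article states the source of the control data, "we request data from the Federal Statistical Office to provide a nationwide comparability", and the outcome taken from it: "We will use data on length of hospital stay". The other variables named there are for adjustment. The Discussion describes the same group as "using administrative data from non-participating hospitals as a control group".

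Both models are written for length of stay and use these controls. Under Difference in differences: "We will test for interaction between the intervention period and the intervention population". The ITS section lists four tests. Tests (ii) and (iiii), as numbered there, compare trends or changes in trend between control and intervention populations. The section then closes with "These models will also be implemented for the analyses of the secondary endpoints", without restriction.

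The general analysis section adds "We will compare all endpoints between all three study phases". The Endpoints section lists seven secondary items. A separate paragraph then adds process measures: the professions' compliance and agreement in using the tool, and "delays from the anticipated to the effective discharge date as compared to discharge date anticipated by the different health care professionals".

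**The concern.** A controlled model needs the same outcome in both groups. If only the study hospitals have it, the model becomes a within-hospital analysis and no longer separates the tool's effect from background change.

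This matters because the trial's hypothesis has two parts: a shorter stay, and no loss in patient outcomes or functional independence. The second part rests on the secondary endpoints. The Discussion gives the administrative control group as the answer to the lack of randomization, and the Background acknowledges secular falls in length of stay. As stated, that protection covers length of stay only. The closing ITS sentence invites a reader to assume that the no-harm evidence has the same protection.

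**Working it through.** The article gives no figure to reproduce here, so the check sets what the models need against what the data supply.

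**1. What the models need.** Ignoring covariates, the difference-in-differences model is

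E(Y) = b0 + b1·Group + b2·Period + b3·Group×Period,

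with b3 = (change in study hospitals) − (change in control hospitals). If Y exists only in study hospitals, Group = 1 for every record, and Group×Period is identical to Period. Only the sum b2 + b3 can be estimated, so b3 is not identified. ITS tests (ii) and (iiii) fail for the same reason. Test (i), a trend within a period, and test (iii), a change in trend between observation and intervention phases, can be run in the study hospitals alone.

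**2. What the controls supply.** One outcome is named, length of stay.

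**3. The seven listed secondary items** (Endpoints; User-oriented key data benchmarking; Control population).

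| Item | Control series |
|---|---|
| Mortality, in hospital and at 30 days | None stated |
| Unplanned readmissions; unplanned GP or ED visits | Readmissions: none stated. Visits: not possible, as they rest on the interview |
| Factors delaying ED and ward flow | None stated |
| Waiting time from transfer request to transfer | None stated |
| Institutionalization | None stated |
| Satisfaction | Not possible, interview only |
| Functional status, EQ-5D | Not possible, interview only |

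The count of items with a stated control series is 0 of 7. For two items and part of a third, the gap follows from the design: the interviews are held with included patients, by a local team at each study site. For the rest, it is only that no control source is stated.

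**4. What remains feasible.** Under Data collection process, records and 30-day interviews are gathered in all three phases at the study hospitals. Tests (i) and (iii) therefore stay available for endpoints from these sources. The observation and intervention phases are season-matched, so a phase comparison is also available.

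**5. Comparison across all three phases.** The Coaching section places use of the new electronic tools in the implementation phase, after the observation phase. Compliance and agreement in using the tool therefore have no observation-phase value by definition. Delay against the discharge date expected by each profession needs that date to be recorded. The Fig. 1 legend describes the ward-round tool as where the professions propose dates, and no observation-phase source is stated. The same legend says of that tool "Also, reasons for delays in discharge are being monitored", but it does not say that the tool is the only source.

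**The case against.** The strongest reply has four parts.

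- **The models sentence follows four tests, two of which need no controls.** This stands. A reader might infer that the secondary analyses cannot be done at all. The documents do not support that, because only the control-based part fails. Whether the sentence also takes in the difference-in-differences model, described one section earlier, is a matter of reading. Tests (ii) and (iiii) are affected either way.
- **The article does not say that length of stay is the only field obtained for controls, and a condensed article may leave the mapping of endpoints to sources to the full protocol.** This stands in part. For mortality, readmission and institutionalization, the most one can say is that no control series is stated. It does not help the interview endpoints, which administrative data from non-participating hospitals cannot supply.
- **The tool-dependent measures are not in the list of secondary endpoints.** This stands. A reader might infer that several listed secondary endpoints exist only once the tool runs. Of the seven, only delay factors have a visible link to the tool, and that item also covers ED flow and may be recoverable from records. The process measures conflict instead with the promise to compare all endpoints across all phases, since they are in the Endpoints section.
- **The tool already runs in the implementation phase.** This stands. What is missing is an observation-phase series, not every series before the intervention phase.

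**Conclusion.** The point holds in a limited form. For satisfaction, EQ-5D and unplanned GP or ED visits, the difference-in-differences interaction and ITS tests (ii) and (iiii) cannot be estimated, so the blanket sentence cannot be carried out for them. For mortality, readmission and institutionalization, no control series is stated. The all-phase comparison cannot be done for compliance and agreement in tool use, and has no stated observation-phase source for delay against the professions' expected discharge dates.

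This rests on two readings: that length of stay is the only control outcome because no other is named, and that GP and ED visits come from the interview. No bias can be quantified from the documents. A reader might also infer that uncontrolled results will be reported as controlled ones. Nothing in the article says so, and it lists non-randomization as a limitation. The consequence is that the no-harm half of the conclusion has weaker support than the wording suggests. The length-of-stay models are not the subject of this point.

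**What to change.** Replace the closing sentence of the ITS section with three rules.

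- **Endpoints with control data.** Add in-hospital death, discharge destination and, if stays can be linked, readmission to the Federal Statistical Office request. Analyse those obtained with the difference-in-differences model and the controlled ITS. That the office can supply them is an assumption to confirm before the rule is fixed.
- **Interview endpoints and any others without control data.** Use a single-group ITS within the study hospitals, tests (i) and (iii), plus the season-matched comparison of observation and intervention phases. Label both as uncontrolled and word the no-harm conclusion to match.
- **Tool-generated process measures.** Report them descriptively for the implementation and intervention phases, and exempt them from the comparison of all endpoints across all three phases.

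The cost is a slightly larger data request, some wording, and weaker claims for the interview endpoints. No new data collection at the study sites is needed.
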